**11.2 Secondary Efficacy:**

1) Rate of patients with negative SARS-CoV-2 on nasal or throat swab in a 2-day continuous real time RT-PCR test beginning from ‘first day of clinical recovery’ (see above) or ‘Day 10 after onset of symptoms depending on whichever of the two time points is first achieved

2) Timelines (days counted from onset of illness) - normal body temperature <37◦C, absence or minimal cough (see ‘clinical recovery’ for the definition), absence of dyspnoea (respiration rate 24/minute or less on room air), onset of clinical pneumonia, pneumonia diagnosed on chest X-Ray or CT scan, time to supplemental oxygen, admit in intensive care unit, mechanical ventilation (non-invasive), mechanical ventilation (invasive), steroid use, respiratory failure, adult respiratory distress syndrome, cytokine storm syndrome, secondary infection, shock, septicaemia shock, hospital discharge, death, negative nose or throat swab confirmatory test, all-cause mortality (Time Frame: up to 28 days).

Note: In case of symptoms, the absence on improvement should be sustained for at least 72 hours or live hospital discharge, whichever comes first.

3) Proportion OF patients developing an event that reflects clinical or otherwise improvement of worsening (the events are similar to those listed under Timelines, see above)

4) Improvement on pulmonary function tests using simple ‘home expiratory spirometer’ device and peripheral pulse oximetry

5) Improvement in selected laboratory parameters: blood haemoglobin, differential and total leukocyte counts, liver enzymes, renal functions, acute phase reactants, serum IL-6 and other selected cytokines, serum muscle enzymes (CK, CPK), serum ferritin, serum d-Dimer, anti-oxidant markers, serum BNP (cardiac function)

6) Serological Protective Antibody Assay (IgM and IgG)

7) Radiological Improvement on digital chest Xray and HRCT chest

8) Drug related: side effects and toxicity, and tolerability

9) Health status: WHO QOL (Appendix M) brief, health related behaviour habit and fitness questionnaire based on visual analogue scale (See Appendix N)

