**17.2 Statistical Analysis:**

Whenever suitable, both completer and an intent-to-treat analysis with ‘last observation carried forward’ will be performed; for intent-to-treat analysis the patient should have completed at least 4 weeks of intervention and completed the follow up visit at 4 weeks post enrollment.

All statistical processing will be performed using SPSS & BMDP software unless otherwise stated.

The data will be individually analyzed for central tendencies (mean, median), range, standard error, standard deviation and 95% confidence intervals for each intervention arm in each of the groups in the study. Data will be tabulated and graphically shown using standard format and MS Excel and other software programs. Though ANOVA will be used for most of the measures, standard parametric (Student t-test) and non-parametric statistical tests (Mann Whitney statistic, Kruskal Wallis test) will be used depending upon the normality of the data. Fisher’s exact test or Chi Square will be used to test the proportion of patients classified as efficacy failures and those with AE (calculate exact binomial 95% Confidence Interval).

The primary efficacy measures of ‘mean time to clinical recovery’ and ‘proportion of patients with clinical recovery’ in the two arms will be compared using appropriate statistical tests; ANOVA for ‘mean time’ and two proportion z-test for proportion of patients.

Secondary efficacy measures in the two arms will also be compared and Bonferroni correction will be applied for multiple comparisons.

Risk ascertainment will be done for selected variables. Regression analysis (multivariate and step down) will be used to identify predictors for important outcomes. Survival analysis will be carried out to compare the two interventions (HCQ and Ashwagandha) for primary efficacy at different study time points.

Within arm efficacy will be evaluated by a one sample Student t-test.

Significance for each statistical test result will be considered at two-sided p< 0.05.

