***Katuki (Picrorhiza kurroa RoyluxBenth– Root)***

1. Anti-inflammatory effect by l3-adrenergic blockade (26)
2. Stimulate the cell-mediated and humoral components of the immune system as well as phagocytosis in experimental animals (27, 28)
3. Improves the immune system by increasing the proliferation of lymphocytes and cytokine levels (IL-4 and IFN-gamma) in serum, in HA titre, DTH, PFC, phagocytic index and CD4/CD8 population. (29)
4. Another study demonstrates the antioxidant and free radical scavenging activity of the leaf extract of the same plant. (30)
5. Significantly inhibit growth of Plasmodium falciparum (31, 32)

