Cytokines play an important role in immunopathology of viral infections in which a rapid and coordinated innate immune response is often seen as the first line of defense against viral infection. However, dysregulated and excessive immune responses may cause immune imbalance leading to severe systemic inflammatory disorders. Pro-inflammatory responses have reported to play an important role in the pathogenesis of several viral infections (8) including Human Coronavirus (HCoVs)(9). A cytokine profile resembling secondary hemophagocyticlymphohistiocytosis (sHLH) is reported to be associated with COVID-19 disease severity, characterised by increased levels of cytokines and chemokines such as interleukin (IL)-2, IL-7, granulocytecolony stimulating factor, interferon-γ inducible protein 10, monocyte chemoattractant protein 1, macrophage inflammatory protein 1-α, and tumour necrosis factor-α (10). Elevated ferritin levels along with elevated interleukin-6 levels have been reported as significant predictors of fatality in a retrospective, multicentre study of 150 confirmed COVID-19 cases in Wuhan, China, suggesting that mortality might be due to virally driven hyperinflammation (11).High levels of expression of IL-1B, IFN-γ, IP-10, and monocyte chemoattractant protein 1 (MCP-1) have been reported in patients with COVID-19 (10). Positive correlation between serum levels of IL-2R and IL-6 (Cytokine storm) and severity of diseases has been seen in patients with COVID-19 (12). In COVID-19, the inflammatory cytokine storm is closely related to the development and progression of Acute Respiratory Distress Syndrome.

Cytokines can be estimated in the serum of patients by several assays such as ELISA or multiplex assays.  Advances in laboratory technologies including flow cytometrics, Luminex bead-based assays, planar multiplex assays. Although the multiplex platforms and ELISA-based systems exhibit distinct strengths and weaknesses, conventional quantitative ELISA assays are very convenient in clinical settings. Several sandwich ELISA assays using monoclonal antibodies against various cytokines are commercially available wherein the microwell plates are coated with monoclonal antibodies against the cytokine to be estimated in the serum.

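### Improvement in total leukocyte count, which can be abnormal in either direction, is left to tests of location that miss most of a true return to normal

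*Combined protocol and SAP*

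**What the plan says.** Section 11.2, item 5 lists "Improvement in selected laboratory parameters: blood haemoglobin, differential and total leukocyte counts, liver enzymes" among its markers and later adds "serum IL-6 and other selected cytokines". It does not say whether a rise or a fall counts, what range is normal, or on which day the comparison is made. The plan can be specific when it chooses: the SpO2 criterion for clinical recovery has a numerical cut-off.

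Section 17.2 supplies the tests: "Though ANOVA will be used for most of the measures, standard parametric (Student t-test) and non-parametric statistical tests" are to be used according to normality. It adds "Within arm efficacy will be evaluated by a one sample Student t-test" and "Secondary efficacy measures in the two arms will also be compared and Bonferroni correction will be applied for multiple comparisons", without giving the number of comparisons. Fisher's exact or chi-square tests are named for efficacy failures and adverse events, and a z-test for the primary proportion. No analysis of return to a normal range is described for any laboratory marker.

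Table 5 (Section 2.2) reports leucopenia (below 4000/mm³) in 38%, 9%, 17% and 25% of patients in the four series that give it, and leucocytosis (above 10000/mm³) in 6%, 24%, 21% and 30% of the same series. Lymphocytes are tabulated only as low.

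On IFN-gamma, Appendix D says of one AYUSH 64 ingredient: "Improves the immune system by increasing the proliferation of lymphocytes and cytokine levels (IL-4 and IFN-gamma) in serum". Appendix O, in a discussion of excessive and harmful immune responses, says: "High levels of expression of IL-1B, IFN-γ, IP-10, and monocyte chemoattractant protein 1 (MCP-1) have been reported in patients with COVID-19".

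**The concern.** For a marker that is too low in some patients and too high in others, improvement means movement towards the middle. ANOVA, the t-test and the Mann-Whitney test ask whether one arm's values lie higher or lower than the other's. A drug that does what is hoped pulls the two tails in opposite directions, and what is left for these tests is the imbalance between the tails.

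Two consequences follow. A null result for total leukocytes would say little about whether the drug helped. A positive result could be a rise or a fall for the same benefit, depending on who was enrolled. Appendix C adds to the ambiguity by presenting leucocytosis as part of a favourable immune effect of Tinospora, while Table 5 lists it as an abnormality of the disease.

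Secondary objective 1 is the effect on surrogate markers. In an exploratory trial with no power calculation, such markers help to decide what to pursue next.

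**Working it through.** **The plan's own figures.** Section 17.1 gives 70 per arm by convenience, with no effect size, SD or power, so there is no stated calculation to reproduce. It expects 15-20% withdrawal, which leaves 70 × 0.85 = 59.5 to 70 × 0.80 = 56 per arm.

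**Inputs.** The low and high percentages come from Table 5. The following are assumptions, not document figures: group means of 3.3 (low), 6.8 (normal) and 12 (high) × 10⁹/L, the SDs, and normalisation of 80% of abnormal counts on the drug against 40% on standard of care.

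**Expected arm difference in mean change.** A low count that normalises rises by 6.8 − 3.3 = 3.5; a high one falls by 12 − 6.8 = 5.2. Write L = 3.5 × proportion low and H = 5.2 × proportion high. The arm difference is (0.8 − 0.4) × (L − H), and the share of the movement that cancels is 1 − |L − H|/(L + H).

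| Series (n) | Low | High | L | H | Arm difference | Cancelled share | Low per high patient |
|---|---|---|---|---|---|---|---|
| 1099 | 38% | 6% | 1.33 | 0.31 | +0.41 | 38% | 6.3 |
| 99 | 9% | 24% | 0.32 | 1.25 | −0.37 | 40% | 0.38 |
| 191 | 17% | 21% | 0.60 | 1.09 | −0.20 | 71% | 0.81 |
| 41 | 25% | 30% | 0.88 | 1.56 | −0.27 | 72% | 0.83 |

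The same true benefit appears as a rise in one mix and a fall in the other three. Complete cancellation would need 5.2/3.5 ≈ 1.5 low patients per high patient, and none of the four mixes has that.

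**Power by simulation** (70 per arm, two-sided alpha 0.05 before Bonferroni, range over the four mixes and over different assumed SDs):

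- location tests (t-test on change, t-test on follow-up values, Mann-Whitney): roughly 5-25%, highest in the 38%/6% mix;
- Fisher's exact test on return to range: about 75-95%;
- distance outside the range, all patients, compared by a rank test: about 65-90%. A t-test on the same distances does less well.

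**Sensitivity.** With assumed means 3.2/6.5/13 and 90% against 40% normalising, location tests reach 5-38% and the proportion outside the range 85-98%. With 56 per arm these become 5-31% and 73-96%. Under the first set of assumptions, with 57 per arm and Bonferroni over an assumed 20 markers, the return-to-range test falls to about 23-55%.

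**Cytokine direction.** If either direction may be read as improvement, the chance of a false benefit on one marker is 5%; with the direction fixed it is 2.5%. Over the nine cytokines in Appendix A, treated as independent, Bonferroni at 0.05/9 gives 1 − (1 − 0.05/9)⁹ = 4.9%, against 2.5% with directions fixed.

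**The case against.** The strongest reply has several parts.

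*The source cohorts are sicker than this trial.* Table 3 gives ARDS in 31% and shock in 59% of the 191-patient series, and ARDS in 29% of the 41-patient series; this trial excludes severe disease. The 1099-patient series (3% ARDS, 1% shock) is probably closest, and there cancellation is smallest and the location tests do best. This stands: the figures illustrate the problem and do not predict power here. Even in that mix, the location tests remain far below return to range.

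*Opposite tails are not the only cause of low power.* With 44% low counts and none high, a t-test on change still reaches only about 52% against 87% for return to range, because normal patients dilute the mean. This also stands, but it is a second reason to prefer a measure of distance from normal.

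*Section 17.2 allows rank tests and names no test for item 5.* True, but rank tests also compare location and lie in the same low range.

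*A reader might infer that normalisation cancels out altogether.* It does not. Counting heads suggests near-complete cancellation in two series, but only if upward and downward moves are equal in size; under the assumed means it is 38-72%.

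*A reader might also infer that the cytokine comparisons cannot fail, or that any change could be claimed as benefit.* The documents do not support that. Testing is two-sided at 0.05 with Bonferroni for secondary measures. IL-6, the only cytokine named in item 5, has a clear direction, since the documents tie its elevation to severity and death. For IL-4 only the favourable reading of a rise appears, so there is no conflict. For IFN-gamma, that a rise is harmful is inferred from the setting of the Appendix O sentence, which reports high levels in patients and does not say outright that a rise is bad.

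*These are secondary outcomes in an exploratory trial.* This limits the weight of the point, but the remedy is cheap.

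**Conclusion.** The point holds for total leukocyte count. Improvement is undefined, the marker is abnormal both ways in all four series that report it, and the stated tests are insensitive to a return to normal: roughly 5-25% power against about 75-95% for return to range and 65-90% for distance outside the range. The sign of the arm difference also changes with case mix. These figures rest on assumed group means, SDs and normalisation rates, full enrolment and uncorrected alpha.

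It does not extend to every differential count: for lymphocytes the documents show only low values, so a one-direction definition is enough. For cytokines the gap is narrower: no direction is written down for most of them, and IFN-gamma is described in ways that invite interpretation after the result is known. No primary outcome is affected. The change should be made, but it is not critical to the trial.

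**What to change.** - **Total leukocyte count.** State the reference range and a fixed day. Compare distance outside the range (zero if inside) between arms in all patients, by a rank test. As support, report the proportion of baseline-abnormal patients who are back in range. The chosen day should not depend on discharge: the Appendix A note merges week 4 or week 8 tests with discharge when the two fall within two weeks, so those values need not come from a common day.
- **Lymphocytes.** State that a rise from a low count is improvement.
- **Cytokines.** Before data lock, write down for each one the direction that counts as improvement. For IFN-gamma, report change descriptively and do not label it improvement.
- **Multiplicity.** List the markers, so that the Bonferroni divisor is known.

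The cost is SAP text and one derived variable per marker; no new samples are needed. The drawback is that the responder analysis uses only patients abnormal at baseline. At the Table 5 rates that is 70 × 0.33 ≈ 23 to 70 × 0.55 ≈ 39 per arm before withdrawal, and probably fewer in a milder population. That is why the all-patient distance should lead.

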# 12. AYURVEDIC MEASURES

**Baseline**:

a) Prakriti

b) Clinical Features

c) Ayurvedic Disease Subtypes / Stages

**Follow Up / Monitoring**:

a) Clinical Features:

b) Ayurveda examination:

c) Ayurvedic Disease Subtypes / Stages

# 13. LABORATORY & OTHER INVESTIGATIONS

These are common to the each of the three Ayurveda formulation drug trials:

1. Blood/Serum (routine): Haemogram, Platelet count, Total leukocyte differential count, Hemoglobin and ESR, Blood sugar level (Fasting), Liver function test and Liver Enzymes (SGOT,SGPT, Alkaline Phosphatase), Renal functions (Serum creatinine, Blood Urea Nitrogen), Lipid profile (Total cholesterol, HDL cholesterol, LDL cholesterol, Triglycerides, VLDL)
2. Serum (inflammatory markers, organ damage):C-Reactive protein titer, lactate dehydrogenase, ferritin, Pro-Calcitonin, Troponin, D-Dimer,
3. Special tests: Blood for Vitamin D, Vitamin B12, Oxidation Biomarkers (Superoxide Dismutase (SOD), Glutathoine (GSH)
4. Cytokine Panel: Interleukin (IL) IL-2, IL-1 beta, IL-4, IL-6,IL-10, IL-13, IL-17, TNF-α, Monocyte Chemotactic Protein-1 (MCP), Interferon gamma, TGF-bet
5. Serum Protective Antibody Response: IgM and IgG against SARS-CoV-2
6. Routine Urinalysis, Urine Pregnancy Test for women of child bearing potential
7. Confirmatory Diagnostic Test: Nasal and/or Throat swab for real time RT-PCR for SARS-CoV-2 (See Appendix O)
8. Other Investigations: USG Abdomen and Pelvis, ECHO-Color Doppler and 12 Lead ECG

Chest X-ray, HRCT scan Chest

**13.1** Rationale for Cytokine Assay: Cytokine assay can be used to study important anti-viral effects (gamma interferon), immune mediated inflammation (IL-6, anti-TNF, IL-17), TH 1 and TH 2 immune response and antibody producing B cell activity (Il 4, IL 13), activation of immune cells such as macrophage activation (MCP). Intense up regulation and elevation of IL 6 and several other cytokines has been reported by several clinical case series and research in COVID-19 and can guide specific therapy (as in case of use of monoclonal antibody to IL-6 receptor being used to treat Cytokine storm in COVID 19).

Detail methods for diagnostic tests, serology and cytokine assay are described in Appendix O.

# 14. SAFETY ISSUES AND ENDPOINTS, ADVERSE EVENTS

All adverse events will be recorded and meticulously followed till resolution. Serious adverse events will require immediate action and further communication by the study investigator. AE will be classified by the study physician as described in Appendix P and classified as shown in Appendix Q and recorded in the AE form by the investigator along with its grading (Appendix R).

A-priori check list of common drug related side as a ready reckoner will be provided to all investigators so that timely action may be taken if a patient reports any kind of adverse event that may be related to the study intervention. The patients will be encouraged to record any kind of symptom that they may think is due to a drug in their personal diary which will be scrutinized by the study physician at monthly visits and on completion.

The following ‘**Stop rules’** will be applied to withdraw the patient prematurely because of safety concerns:

1. Patients developing severe COVID-19 as described above under the ‘exclusion criteria’
2. Requiring hospitalization for disorders other than COVID-19 will be critically evaluated by the study physician to decide continuity in the study
3. Any adverse clinical or lab profile that in the opinion of the investigator is likely to be due to therapeutic intervention and threatens to deteriorate the wellbeing of the patients

Data Safety Monitoring Board (DSMB) will be established to monitor safety of the participants and assess safety data. The CONSORT extension for HARMS will be used to document and report safety data.

# 15. STUDY PROCEDURES: TIMELINES AND EVENTS SCHEDULE

The overview is shown in Table 1.

15.1 Baseline Visit: (Visit 1)

Patients who meet the criteria for selection, must have the following procedures completed during this visit prior to study entry.

Visit 1 (Baseline)

|  | Providing with Patient Information Fact Sheet for thorough study. |
| --- | --- |
|  | Signing of Informed Consent. |
|  | Complete medical examination form: medical history, comprehensive physical examination, co-morbidity, medication history. |
|  | Symptom Assessment, Vital Parameters |
|  | Record Baseline Symptoms |
|  | Comprehensive Ayurvedic evaluation. |
|  | Laboratory work up- general health and advanced test and cytokines as in Appendix O |
|  | Ultrasound abdomen and Pelvis, Chest X-ray, HRCT chest, |
|  | Colour Doppler and 12 Lead ECG |
|  | Pulse Oximetry |
|  | Health Related-Behaviour Fitness (HR-BHF) VAS questionnaire, Self-Reported Questionnaire (Mobile app) |
|  | Dispense study medication and begin medication log entry |

15.2 Visit 2 (Day 4):

|  | Symptom Assessment, Vital Parameters |
| --- | --- |
|  | Brief Ayurvedic Evaluation |
|  | Health Related-Behaviour Fitness (HR-BHF) VAS questionnaire, Self-Reported Questionnaire (Mobile app) |
|  | Laboratory work up |
|  | Chest X-ray, HRCT chest, |
|  | Pulse Oximetry |
|  | Monitor Adverse Events |

15.3Visit 2 (Day5 up to-Discharge) (Daily Assessment):

|  | Symptom Assessment, Vital Parameters |
| --- | --- |
|  | Brief Ayurvedic Evaluation |
|  | Laboratory work up |
|  | Pulse Oximetry |
|  | Monitor Adverse Events |
|  | Colour Doppler, ECG |
|  | Chest X-ray, and HRCT chest |
|  | Health Related-Behaviour Fitness (HR-BHF) VAS questionnaire, Self-Reported Questionnaire (Mobile app) |
|  | Completion and Outcome Report |

15.4DISCHARGE

|  | Symptom Assessment, Vital Parameters |
| --- | --- |
|  | Brief Ayurvedic Evaluation |
|  | Laboratory work up |
|  | Pulse Oximetry |
|  | Monitor Adverse Events |
|  | Colour Doppler, ECG |
|  | Chest X-ray, and HRCT chest |
|  | Health Related-Behavior Fitness (HR-BHF) VAS questionnaire, Self-Reported Questionnaire (Mobile app) |
|  | Completion and Outcome Report |

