# APPENDIX

## Appendix A: Schedule of Events

**Table 1: SCHEDULE OF EVENTS:**

| VISIT | Baseline | D 4 | Day 4 Discharge | Discharge | Week 4 | Week 8 | Week 12 | Remarks |
| --- | --- | --- | --- | --- | --- | --- | --- | --- |
| Informed Consent,  Selection Criteria, Demographics, Disease Features, Baseline Symptoms | X |  |  |  |  |  |  |  |
| Medical History and Comprehensive Physical Examination | X |  |  | X |  | X | X |  |
| Symptom, Vital Parameters | X |  |  |  |  |  |  |  |
| Adverse Events **^a^** |  | X | X | X | X | X | X | X |
| AyurvedicEvaluation**^b^** | X |  | X |  | X | X | X |  |
| Pulse Oximetry**^c^** | X | X | X | X | X | X | X |  |
| USG Abdomen and Pelvis | X |  |  |  |  |  |  |  |
| Color Doppler and 12 Lead ECG | X |  |  | X |  |  |  |  |
| Chest X-ray | X | X | X | X |  |  |  |  |
| HRCT Chest | X | X |  | X |  |  |  |  |
| Pregnancy Test | X |  |  |  |  |  |  |  |

| VISIT | Baseline | Day 4 | Day 4- Discharge | Discharge | Week 4 | Week 8 | Week 12 | Remarks |
| --- | --- | --- | --- | --- | --- | --- | --- | --- |
| Hb, TLC, DLC, Platelet, Urine ®**^d^** | X |  | X |  | X | X | X |  |
| ESR and CRP**^e^** | X |  | X |  | X | X | X |  |
| LFT, BUN, SrCreatinine**^f^** | X |  | X |  | X | X | X |  |
| Lipid Profile | X |  |  |  | X |  | X |  |
| LDH, Ferritin**^g^** | X |  | X |  | X |  | X |  |
| IL-6 Pro-cal**^h^** | X |  | X |  | X |  | X |  |
| CK, BNP, Troponin,  D-Dimer **^i^** | X |  | X |  | X |  | X |  |
| Na, K, Cl, Fe, Zn, Mn, Vitamin D , B12 | X |  |  | X |  |  | X |  |
| Oxidation Biomarkers  -SOD, GSH | X | X |  | X |  |  | X |  |
| Cytokine Panel**^J^** | X |  |  | X |  |  | X |  |
| Serum Immune Response**^k^** | X | X | X | X | X | X | X |  |
| Health Related-Behaviour Fitness (HR-BHF) VAS questionnaire, Self Reported Questionnaire (Mobile app)**^L^** | X | X | X | X | X | X | X |  |
| Dispense study medication**^m^** | X |  |  |  |  |  |  |  |
| Completion report |  |  |  | X |  |  | X |  |

Footnotes:

1. Symptom Assessment, vital parameters and monitoring of adverse events to be performed daily by Physician
2. Daily Ayurvedic Monitoring till discharge by Ayurvedic Physician and subsequently for 4, 8 and 12 week.
3. Pulse oximetry to be performed daily

d-f: These tests should be performed at Baseline and once in 3 days till discharge and in addition as per discretion of the treating physician

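### Section 15.3 repeats the discharge checklist under a daily heading, so as written it calls for daily HRCT, Doppler/ECG, laboratory work and completion reports that Table 1 does not schedule

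*Combined protocol and SAP*

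**What the plan says.** Section 15 sets out procedures visit by visit. The in-hospital period after Day 4 is covered by Section 15.3, headed "15.3Visit 2 (Day5 up to-Discharge) (Daily Assessment". Its nine rows are symptoms and vital parameters, brief Ayurvedic evaluation, laboratory work, pulse oximetry, adverse events, Colour Doppler and ECG, "Chest X-ray, and HRCT chest", the HR-BHF and self-report questionnaires, and a completion and outcome report. Section 15.4 (discharge) has its own list.

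Table 1 in Appendix A has separate columns for Day 4, for Day 4 to discharge, and for discharge. Its rows for three of these items read "HRCT Chest | X | X | | X", "Color Doppler and 12 Lead ECG | X | | | X" and "Completion report | | | | X | | | X". In each, the cell for Day 4 to discharge is blank.

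The footnotes to Table 1 say what is daily: "Symptom Assessment, vital parameters and monitoring of adverse events to be performed daily by Physician", "Daily Ayurvedic Monitoring till discharge by Ayurvedic Physician", pulse oximetry (footnote c) and the mobile-app symptom record (footnote L). Footnotes d to i put the routine haematology, biochemistry and marker tests at every third day until discharge, with extra tests left to the treating physician.

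Two other places bear on precedence. The section on clinical evaluation including Ayurvedic assessment says that laboratory and imaging tests follow Table 1, and places the completion form at the end of treatment and discharge. Section 15 opens by referring to Table 1 for the overview.

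**The concern.** The visit-by-visit list and the schedule give different instructions for the same days. A site working from 15.3 would order chest CT, Doppler and ECG, and laboratory work every day for patients with mild to moderate disease, and would file a completion report each day. The schedule intends none of this. What is at stake is avoidable radiation, burden and cost.

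There is also a compliance problem that does not depend on any extra scan being done. Section 18.1 forbids deviations except in an emergency, and Section 19.6 has monitors check protocol compliance. A site that follows Table 1 departs from 15.3, and a site that follows 15.3 departs from Table 1. No sentence in the protocol says outright which of the two prevails.

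**Working it through.** No planned figure is involved, so the check is a comparison of the lists followed by a count.

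**Step 1: 15.3 against 15.4.** All 9 of 9 rows match, in the same order. The only difference is the spelling of behaviour in the questionnaire row. Section 15.3 also reuses the visit number of the section before it ("15.2 Visit 2 (Day 4"). No Visit 3 exists, and Week 4 is Visit 4.

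**Step 2: Section 15 against Table 1.**

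| Item | 15.1, 15.2, 15.4 to 15.7 | 15.3 | Table 1 |
|---|---|---|---|
| HRCT | baseline, Day 4, discharge | daily | baseline, Day 4, discharge |
| Doppler/ECG | baseline, discharge | daily | baseline, discharge |
| Completion report | discharge, Week 12 | daily | discharge, Week 12 |

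For these three items every other subsection of Section 15 agrees with Table 1. Section 15.3 is the only outlier.

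**Step 3: which 15.3 rows are meant to be daily.** Footnotes a, b and c make four rows daily: symptoms and vitals, adverse events, Ayurvedic evaluation and oximetry. One row is daily in part: in footnote L the daily instruction attaches to the mobile app, not to HR-BHF, which asks about the past week (Appendix N). The remaining four rows have no daily instruction: laboratory work, Doppler/ECG, X-ray/HRCT and the completion report. That gives 4 + 1 + 4 = 9.

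**Step 4: size if 15.3 alone were followed.** Section 8 expects most patients to go home after 5 to 15 days in hospital. Assume that baseline is the day of admission, days are counted from admission, discharge is on Day d, and discharge-day procedures are counted once. Days 5 to d − 1 contribute d − 5 extra occasions.

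- HRCT: baseline 1 + Day 4 1 + (d − 5) + discharge 1 = d − 2
- Doppler/ECG: baseline 1 + (d − 5) + discharge 1 = d − 3
- Completion reports up to discharge: (d − 5) + 1 = d − 4

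| Discharge day | HRCT (Table 1: 3) | Doppler/ECG (Table 1: 2) | Reports (Table 1: 1) | Excess of each |
|---|---|---|---|---|
| 5 | 3 | 2 | 1 | 0 |
| 10 | 8 | 7 | 6 | 5 |
| 15 | 13 | 12 | 11 | 10 |

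Chest X-ray is not counted, because Table 1 does tick it between Day 4 and discharge, though without a frequency. No laboratory excess is counted either: 15.3 does not say which tests its laboratory row covers, and the footnotes allow extra tests at the physician's discretion. The conflict there is simply daily against every third day.

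**The case against.** The best reply is that the protocol already answers the question. The clinical evaluation section sends laboratory and imaging tests to Table 1 and puts the completion form at discharge. Section 15 itself points to Table 1. The form that sites fill in each day (Appendix J) has printed rows for symptoms, vitals and complications, and none for HRCT, Doppler, ECG or laboratory results. Section 19.12 plans meetings and SOPs to make procedures uniform. A daily completion report is also so implausible that a site would probably notice the error. Most of this stands, and it is why the point is minor.

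The list might also be read as collecting whatever falls due at some time before discharge. The heading works against that, since it calls the assessment daily, and discharge procedures have their own list in 15.4.

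Two stronger readings are tempting. A reader might infer that the trial plans daily CT. The documents do not support this: Table 1, the other subsections of Section 15 and the clinical evaluation section all contradict it. A reader might also infer a threat to the results. Clinical recovery, the basis of both primary outcomes, is defined in Section 11.1 without imaging, the list applies to both arms alike, and nothing in it touches sample size or error rates.

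**Conclusion.** This is an internal inconsistency that calls for a minor correction. Section 15.3 is wrong as written for HRCT, Doppler/ECG and the completion report, and it conflicts with footnotes d to i on laboratory tests. That it arose by copying is an inference, but a strong one: the lists are identical, the visit number is duplicated, and a daily completion report serves no purpose.

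The excess of 0 to 10 HRCTs per patient is a worst case. It rests on the day-counting assumptions above and on a site following 15.3 while ignoring the references to Table 1. Under Table 1 the excess is 0.

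**What to change.** In Section 15.3:

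- Delete HRCT, Colour Doppler/ECG and the completion and outcome report.
- Keep as daily: symptoms and vitals, Ayurvedic evaluation, pulse oximetry, adverse events and the mobile-app symptom record. Take HR-BHF out of the daily list; 15.2 and 15.4 already place it at Day 4 and discharge.
- Mark routine laboratory tests as every third day under footnotes d to i, with cytokines and serology on the days in footnotes j and k.
- State a frequency for chest X-ray between Day 4 and discharge, for example only when clinically indicated. Pointing to Table 1 is not enough here, because its tick carries no frequency.
- Correct the duplicated visit number.

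At the start of Section 15, state that Table 1 governs the timing of tests and of the completion report, and that its footnotes prevail over its cells where they differ. The second part is needed because the cytokine row is blank between Day 4 and discharge and at Week 8, while footnote j requires Days 5, 10 and 15 and Week 8. Limit the sentence to tests and reports: footnote m on dispensing names Week 12, where 15.5 and 15.6 dispense at Weeks 4 and 8, and should be settled separately.

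The cost is protocol wording, submitted as an amendment. It adds no visit, requires no test that the table or its footnotes do not already call for, and changes no outcome definition.
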